## Introduction

### Background and rationale {6a}

In recent years, noninvasive ventilation (NIV) has increasingly become a common approach for the treatment of hypercapnic [1, 2] and hypoxemic [3] patients both inside [3] and outside [4–6] the intensive care unit (ICU). NIV refers to the delivery of a positive pressure to the patient through interfaces like masks or helmets without the need for invasive endotracheal intubation [7]. These interfaces can efficiently and non-invasively support patients with acute respiratory failure (ARF), preserving airway defense mechanisms, speech, and swallowing, averting the need for prolonged sedation, lowering the occurrence of ventilator-associated pneumonia [8], and ultimately reducing ICU admission [9] and mortality [2]. Nonetheless, NIV failure is observed in 8% of hypercapnic [10] and 50% of hypoxemic patients [11], leading to delayed initiation of invasive ventilation treatment and poor outcomes [5, 10, 12, 13].

As patient comfort is a major factor for NIV success [14], the selection of the most suitable interface type is of paramount importance [15]. Another key variable that should be taken into account to achieve patient comfort and avoid the generation of skin breakdown until pressure ulcers, a frequently observed NIV side effect [7], is the time of exposure to a given interface. Indeed, when the pressure applied between the interface and the skin exceeds the capillary pressure, skin breakdown may occur, resulting in NIV discontinuation due to pain and intolerance [16]. Published incidence rates of facial pressure ulcers associated with NIV masks range from 2 to 31% [17–22] depending on the type of mask used, length of treatment, ventilator setting, humidification, nutritional status, and preventative measures adopted.

The development of pressure ulcers is associated with adverse outcomes that may contribute to patient pain and suffering, impaired quality of life [23], and increased hospital costs [24, 25].

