### Sample size {14}

Given a type I error of 0.05, a power of 0.8, an expected proportion of patients who develop pressure sores in the control group of 23% [39], and an expected dropout rate of 5%, 239 subjects per group are estimated to identify a 10% absolute difference in the proportion of patients developing pressure sores between intervention and control groups measured at 36 h from randomization.

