## Assignment of interventions: allocation

### Sequence generation {16a}

Computer-based random sequences will be generated by the statistician in charge of the analyses. A total of 240 random extractions from a Bernoulli distribution with a probability equal to 0.5 will be performed to assign patients 1:1 to the interface rotation (treatment) or standard of care (control) group. Moreover, following the same procedure, patients in the interface rotation group will be assigned to start their treatment wearing an oronasal mask or full face/hybrid masks. The randomization list will be uploaded into the research electronic data capture (REDCap) system that will provide the assigned arm of the patients. Investigators will have no access to the randomization list.

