## Data collection and management

### Plans for assessment and collection of outcomes {18a}

A REDCap database will be set up to collect the information needed for the study. The database will consist of ten sheets. The first one will contain the baseline demographic and clinical characteristics of the patients. Eight sheets will store information on primary and secondary outcomes at each time point. The last one will enlist information on patient discharge and the overall treatment. More specifically, the following variables will be recorded:*Baseline characteristics*: age, sex, hospitalization date, nutritional status, body mass index, Braden scale, frailty index, sensorium (Kelly score), Charlson index, chronic steroids therapy, domiciliary NIV or CPAP, NIV treatment goal.*Outcome assessment:* presence and number of pressure sores, location, comfort score (numerical rating scale from 1 to 5), stage for each lesion, fever, humidification, vasoactive medication, NIV interruption, daily NIV duration, hygiene protocol application, eye irritation, interface change, time interface change, NIV ventilator, circuit type, expiratory positive airway pressure, inspiratory positive airway pressure, leaks, medical treatment for the pressure lesions and eventual skin specialist consult.*Discharge:* discharge date, length of hospital stay, discharge status.

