## Statistical methods

### Statistical methods for primary and secondary outcomes {20a}

The analysis will be performed according to the intention-to-treat (ITT) principle. Descriptive statistics will be calculated to summarize patient characteristics collected at study entry according to the randomization group. Categorical variables will be reported as absolute frequencies and percentages. Continuous variables will be represented as mean and standard deviation or median first and third quartiles if not normally distributed according to the Shapiro–Wilk test.

The raw risk of pressure sore will be calculated at each time point as the ratio between the number of subjects who developed a pressure sore at a given time point divided by the number of subjects undergoing NIV at that time point. Patients having a planned break at the time point considered, but not weaned off NIV, will be considered as patients undergoing NIV.

Mixed effect logistic regression models will be used to estimate the risk of pressure sores and the difference between interfaces, including a random intercept to account for clustering of the subjects within the center and repeated measures within patients. The response variable will be the presence/absence of pressure sores, whereas the independent variables will be the treatment, time (12, 24, 36, 48, 60, 72, 84, 96 h), and their interaction. The marginal predicted probabilities estimated by the model will provide the incidence of pressure sores at different times as well as overall. The inclusion of time as a covariate will allow to test the presence of a time trend in the incidence of pressure sores and to investigate the variation of time trends according to treatment group.

If the descriptive statistics will detect unbalanced characteristics between randomization groups (e.g., indication for NIV), the corresponding variables will be added as covariates in the logistic regression model.

Regarding the number of pressure sores, different mixed effect Poisson regression models will be applied: one for each time point to estimate the average number of pressure sores at each time point and a model in which only the highest number of pressure sores will be considered for each patient. Time will be included as offset to evaluate the average number of pressure sores per day.

The grade and location of pressure sores will be summarized using descriptive statistics at each time point.

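### Baseline covariates enter the pressure-sore model only when the arms look unbalanced, which selects them by chance rather than prognosis and loses a modest amount of power

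*Protocol article*

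**What the plan says.** The protocol article, Statistical methods {20a}, plans a mixed effect logistic regression for presence or absence of pressure sores. Its fixed terms are treatment, time (eight assessments) and their interaction, with random effects for centre and for repeated measures within patients. This is the only inferential model for sore presence in that section, so it is fair to read it as serving the 36 h primary outcome, although it is not labelled primary.

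Baseline characteristics come in by one rule: "If the descriptive statistics will detect unbalanced characteristics between randomization groups (e.g., indication for NIV), the corresponding variables will be added as covariates". Indication for NIV is only an example, and no other section fixes an adjustment set.

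Three other sections bear on the point:

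- Plans for assessment {18a} lists the baseline variables collected, among them "nutritional status, body mass index, Braden scale, frailty index", together with age and NIV treatment goal.
- Background {6a} says that reported ulcer incidence varies "depending on the type of mask used, length of treatment, ventilator setting, humidification, nutritional status, and preventative measures adopted".
- Sequence generation {16a} describes "random extractions from a Bernoulli distribution with a probability equal to 0.5 will be performed to assign patients 1:1" and mentions no stratification, so the design does not restrain chance imbalance.

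**The concern.** A baseline difference between randomised groups is a chance event. What makes a covariate worth adjusting for is how well it predicts the outcome, and the imbalance rule does not look at that. It can bring in a variable unrelated to pressure sores because it drifted apart, and leave out a strong predictor because it did not.

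Two things are at stake. The first is efficiency: in logistic regression, adjusting for prognostic baseline factors raises power, and the design has no slack. The second is that the model is unknown until the arm-level baseline tables are seen. Different reasonable readings of imbalance lead to different models, and the covariate set could differ between the interim look at two-thirds of the sample (Interim analyses {21b}) and the final analysis.

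**Working it through.** **Inputs.** From Sample size {14}: "Given a type I error of 0.05, a power of 0.8"; a control proportion of 23%; the aim to "identify a 10% absolute difference in the proportion of patients developing pressure sores between intervention and control groups", hence 13% under rotation; and "an expected dropout rate of 5%, 239 subjects per group". The final test is assumed two-sided, because only the interim p-value is stated as such. Prognostic strength is not in the documents and is varied below as an assumption.

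**The plan's own figure.** Unpooled variance: 0.23×0.77 + 0.13×0.87 = 0.2902. Then n = 0.2902 × (1.960 + 0.842)² / 0.10² = 227.8, so 228 per arm, and 228/0.95 = 240. The pooled formula gives 231, and 231/0.95 = 244. The stated 239 is reproduced to within 1 and 5 patients respectively. Evaluable patients: 239 × 0.95 = 227 per arm, with unadjusted power of 79.4%.

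**How often the rule fires.** Take 10 to 12 baseline variables as independent, and read imbalance as p<0.05. The chance of at least one hit by chance alone is 1 − 0.95¹⁰ = 40% to 1 − 0.95¹² = 46%.

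**Power at 36 h.** Logistic model, 227 per arm, 23% vs 13%, four independent standard-normal covariates with equal odds ratio (OR) per SD, 4,000 trials per row, Monte Carlo standard error about 0.6 points:

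| OR per SD (assumed) | Unadjusted | Trigger p<0.05 | Trigger standardised difference >0.1 | Prespecified |
|---|---|---|---|---|
| 1.0 | 78.5% | 78.6% | 78.4% | 78.4% |
| 1.3 | 79.2% | 79.6% | 80.5% | 81.2% |
| 1.5 | 79.9% | 80.3% | 80.9% | 83.1% |
| 1.8 | 80.3% | 80.9% | 82.0% | 85.8% |

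Prespecification gains nothing if the covariates are not prognostic. From OR 1.3 to 1.8 it gains 2.0 to 5.5 points over no adjustment, 1.6 to 4.9 over the p<0.05 trigger, and 0.7 to 3.8 over the standardised-difference trigger.

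A separate simulation with one prognostic score (log-odds slope 0.35 to 1.0 per SD) agrees: 79.7–80.2% unadjusted, 79.9–80.3% with the p<0.05 trigger, 80.2–81.6% with the standardised-difference trigger, and 80.9–84.9% prespecified.

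**Type I error.** With no treatment effect, the four-covariate simulation gave 5.0–5.4% with prespecified adjustment and 4.1–5.4% with the triggered rules (Monte Carlo standard error about 0.35 points).

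**How far the model is left open.** With 11 independent baseline variables, four of them prognostic, the p<0.05 reading triggers adjustment in 43% of trials and the standardised-difference >0.1 reading in 97%. Five analyses were compared: unadjusted, p<0.05, p<0.10, standardised difference >0.1 and >0.2. At the design effect they disagree on significance in 6.0%, 7.6% and 9.7% of trials at OR 1.3, 1.5 and 1.8. Under the null, taking the most favourable of the five gave a type I error of about 5.6%.

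**Limit.** These are logistic models at a single time point without random effects. They show the direction and rough size of the effect, not the exact power of the planned longitudinal model.

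**The case against.** Several points on the other side have weight.

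- *A reader might infer that the rule inflates the false-positive rate.* The calculations do not support this. Applied mechanically, the rule holds type I error at or slightly below nominal, and even choosing the best of five readings adds little.
- *A reader might infer that the rule captures almost none of the available gain.* That fits only a significance-test reading, and the protocol names no test. With a standardised difference >0.1, the rule recovers roughly a third to two thirds of the gain in the four-covariate simulation.
- *Discretion is limited.* The wording directs that unbalanced variables be added, and Who will be blinded {17a} keeps data analysts blind to group. This stands in part. Sequence generation {16a} has the statistician responsible for the analyses also generate the allocation sequence, so the protection is incomplete.
- *A threshold or covariate list may sit in a statistical analysis plan that is not shown.* This is accepted, and their absence is not charged here. The criticism is of the imbalance trigger, which the protocol does state.
- *The documents do not show which covariates are strong.* This is also accepted. Most factors named in Background {6a} concern treatment rather than the patient at baseline; nutritional status is the clear baseline factor. No prognostic strength is given for the Braden scale.
- *Adjustment is not free.* Handling of missing data {20c} plans imputation only at 20 to 40% missing, and then as a sensitivity analysis. If missing baseline values removed 5% of patients (227 × 0.95 = 216 per arm), adjusted power in a one-score simulation fell to about 80% for c-statistics of 0.65 to 0.70, which cancels most or all of the gain. The fix has to deal with this.

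**Conclusion.** The point holds as a matter of efficiency and prespecification. The protocol chooses baseline covariates by a criterion unrelated to prognosis, although plausible prognostic factors are already collected. The loss is modest: about 0 to 6 power points against no adjustment and about 0 to 5 against the triggered rules. It is zero if the covariates do not predict sores. The range rests on assumed prognostic strengths, 227 evaluable patients per arm, the design rates of 23% and 13%, and a two-sided 5% test. Besides the power loss, the model is not settled before the data are seen, and reasonable readings of the rule can disagree on significance in some 6 to 10% of trials under the same kind of assumptions. The test itself remains valid. The rule should be changed, but it does not threaten the trial.

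**What to change.** Delete the imbalance trigger. Before any arm-level data are seen, and ideally before the interim analysis, name a short list of baseline covariates from those in Plans for assessment {18a} and include them whatever the observed balance. An example is Braden scale, nutritional status or BMI, age, and NIV indication (collapsed if sparse).

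Expected events are 227 × 0.23 + 227 × 0.13 = 82, so keep to at most about 8 covariate parameters (82/8, about 10 events each). The example uses 1 + 1 + 1 + 3 = 6 if nutritional status is a single score and all four NIV indications are kept.

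Add these terms to the planned mixed model, keeping treatment, time, their interaction and the centre and patient random effects. Report the marginal 36 h risk difference from that model, which builds on the marginal predicted probabilities already planned, and give the model without baseline covariates as supportive. State that missing baseline values will be handled by simple imputation or a missing indicator, so that no randomised patient is dropped on their account.

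The cost is wording in the protocol or analysis plan. No new data are needed.

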### Interim analyses {21b}

A single interim analysis will be performed when two-thirds of the predefined sample are randomized and completed the study. Early stopping criteria will be a predetermined 2-sided *p*-value < 0.01 for the rejection of the null hypothesis that the strategies are equivalent in terms of pressure sore incidence rate.

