### Outcomes {12}

The primary effectiveness outcome is the proportion of patients developing at least one pressure sore of any stage at 36 h from randomization. The reason why this measure of effectiveness was chosen is that it is more clinically relevant than the overall number of pressure sores. Furthermore, 36 h seems to be an appropriate time point given that the time it takes for pressure sores to develop is extremely variable, but it might as well be very short.

Secondary outcomes will be the onset, number, and stage of pressure sores and comfort during NIV measured at different time points (12, 24, 36, 48, 60, 72, 84, 96 h). At the same time points, the location of pressure sores per patient will also be recorded, i.e., forehead, nose bridge, left cheek, right cheek, chin, left periauricular, right periauricular, and occipital. The study will also monitor the number of patients that interrupts NIV due to discomfort, the presence/absence of eye irritation in relation to both oronasal and full face/hybrid mask, poor adherence to the protocol (e.g., duration of NIV treatment/day, interfaces changed and hygiene protocol application both during each 12-h protocol period) and the presence/absence and types of vasoactive medications, i.e., epinephrine, norepinephrine, vasopressin, dobutamine, dopamine, other. Further outcomes include the costs for intervention implementation (e.g., mask-related costs) and those related to the care of pressure sores (antibiotic treatment, specialist medical visits).

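### The efficacy stop at p<0.01 is not reconciled with the stated 5% type I error, and the interim hypothesis does not name the 36 h outcome

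*Protocol article*

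**What the plan says.** **Interim rule** (Interim analyses {21b}): "A single interim analysis will be performed when two-thirds of the predefined sample are randomized and completed the study". Early stopping requires a two-sided p-value below 0.01 "for the rejection of the null hypothesis that the strategies are equivalent in terms of pressure sore incidence rate". The section gives no time point, no level for the final analysis and no spending rule.

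**Error rate and size** (Sample size {14}): "Given a type I error of 0.05, a power of 0.8", a control proportion of 23% and 5% dropout, from which "239 subjects per group are estimated to identify a 10% absolute difference" at 36 h. This is the only place where 0.05 appears as a significance level. The section does not mention the interim analysis.

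**Primary outcome** (Outcomes {12}): "The primary effectiveness outcome is the proportion of patients developing at least one pressure sore of any stage", measured at 36 h from randomization.

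**The concern.** An interim test that can reject the null uses up part of the permitted type I error. If the final test then uses the full 0.05, the chance of a false positive at one look or the other exceeds 0.05. The protocol gives a numeric interim boundary and a numeric type I error but not the final level that would make the two agree.

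The second issue is what the interim test is about. Interim analyses {21b} speaks of a pressure sore incidence rate with no time point, whereas the primary outcome is a proportion at 36 h. The look takes place once patients have completed the study, so data up to 96 h will be in hand. The mixed model in {20a} yields incidence at each of eight time points and overall. The rule should therefore say which of these can trigger a stop.

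At stake are the error rate that the trial can claim and a stopping criterion that reads only one way.

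**Working it through.** **Inputs.** From Sample size {14}: type I error 0.05 (taken as two-sided), power 0.80, 23% against 13%, dropout 5%. From Sequence generation {16a}: 1:1 allocation. From Interim analyses {21b}: one look at two-thirds of the sample (2/3 × 478 ≈ 319 patients), two-sided p<0.01.

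**1. Reproduce the plan's sample size.** With unpooled variance:

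n = (1.960 + 0.842)² × (0.23×0.77 + 0.13×0.87) / 0.10² = 227.8 per group.

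For dropout, 227.8/0.95 = 239.8 and 227.8 × 1.05 = 239.2, so the stated 239 is reproduced. The pooled formula gives 231, or 244 after dropout, which is within 3%. A one-sided 0.05 gives only 192 after dropout, so the plan's figure is two-sided. Putting 1.984 (the adjusted critical value from step 3) in place of 1.960 gives 2.826² × 0.2902 / 0.01 ≈ 231.7, and 231.7/0.95 = 243.9. The plan's 239 therefore goes with the unadjusted level.

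**2. Overall type I error with 0.01 and then 0.05.** Under the null, with the same endpoint at both looks, the two test statistics are approximately bivariate normal with correlation √(2/3) = 0.816:

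1 − P(|Z₁| < 2.576, |Z₂| < 1.960) = 0.0526.

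Equivalently, 0.01 + 0.05 less the probability 0.0074 of rejecting at both looks. Simulated two-arm binomial trials (2,000,000 runs per setting; event risk 18% or 23%; 227 or 239 per group) gave 0.0527 to 0.0535.

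The result depends modestly on timing: 0.0546 if the look fell at half the information, 0.0516 at three-quarters. An interim level of 0.001 at two-thirds would have given 0.0501, so it is the choice of 0.01 that makes the omission count.

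**3. Final level that restores 0.05.** Solving 1 − P(|Z₁| < 2.576, |Z₂| < c) = 0.05 gives c = 1.984, a final two-sided p<0.0473. Rounded down to 0.047, the overall level is 0.0498.

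**4. Power.** Under the design effect the drift is 1.960 + 0.842 = 2.802 at the final look and 2.802 × 0.816 = 2.287 at the interim. The probability of rejecting at either look is:

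| Final boundary | Overall two-sided error | Power |
|---|---|---|
| p<0.05 | 0.0526 | 80.3% |
| p<0.0473 | 0.0500 | 79.6% |

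The cost is about 0.7 points.

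**5. Wording of the interim hypothesis.** Background and rationale {6a} uses *incidence rates* for published figures of 2 to 31%, which are proportions. Statistical methods {20a} uses *incidence* for marginal predicted probabilities at each time and overall. In this document the term is thus compatible with a proportion. What {21b} lacks is the time point.

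**The case against.** **The final level is not stated.** The 0.05 appears only in the sample size section and can be read as the overall level. A statistical analysis plan that is not shown could set a final level near 0.047, and sizing a trial at 0.05 does not fix its final critical value. This stands in part: the unadjusted final test is an inference. But the protocol did not defer the stopping rule. It published the boundary, the timing and the null hypothesis, so it should also publish the level that completes them.

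**The excess is small.** This stands. It is 0.26 percentage points, and only a final p-value between 0.0473 and 0.05 would lead to a different conclusion.

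**The stronger reading on the endpoint.** A reader might infer that the interim tests a different outcome in place of the 36 h proportion, and that the error rate is higher still. The documents do not support this. Their own usage of *incidence* covers proportions, so {21b} omits a time point and does not name another outcome. Any larger error figure would also need an assumed correlation between two different endpoints, which the document does not give. Nor would two endpoints put the error beyond control: 0.01 at the interim and 0.04 at the end would hold it at or below 0.05 whatever their correlation.

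**Conclusion.** The point holds as a minor one. As written, an efficacy boundary of 0.01 at two-thirds of the sample stands beside a type I error of 0.05 with nothing to reconcile them. The overall two-sided error is about 5.26% on three assumptions: the final test uses 0.05, both looks test the 36 h proportion, and the interim falls at two-thirds of the information. The first is implied by the sample size but not stated. Separately, the interim hypothesis is not tied to the 36 h outcome. That is an ambiguity to close, not a proven change of endpoint.

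A reader might also count the overestimation of effect that goes with any early efficacy stop as part of this defect. It comes from having a 0.01 look at all and would be the same after the correction, so it adds nothing here.

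**What to change.** Amend Interim analyses {21b} along these lines: *The interim and final analyses both test the proportion of patients with at least one pressure sore at 36 h, using the same primary 36 h treatment comparison. The interim boundary is two-sided p<0.01 at two-thirds of the information; the final boundary is two-sided p<0.047; the overall two-sided type I error is 0.05.*

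The comparison should be named as the 36 h treatment contrast and not just as the primary model, because the model in {20a} covers eight time points and does not single out 36 h.

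Keep 239 per group, and restate power in Sample size {14} as just under 80% (about 79.6%, against 80.3% with an unadjusted final test). The cost is one sentence, a slightly stricter final threshold and about 0.7 points of power. A plain 0.01 + 0.04 split would also hold the level, but it is stricter than needed: the overall error on the same endpoint would be 0.043.
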